#### Study design

2.3.2

A single-arm, pre–post feasibility study assessing feasibility, acceptability, and change in knowledge associated with a web-based sleep health education course for pediatric healthcare providers.

#### Setting, recruitment, and eligibility criteria

2.3.3

Eligible participants (≥18 years of age) will be recruited from two community-based pediatric healthcare centers affiliated with a large academic medical center in the Northeast (*blinded for review*). Eligible participants are pediatric healthcare providers (MDs, RNs, PAs), including pediatric residents who conduct well-child visits for children aged 5–12 years, who will be recruited from two affiliate community health centers. Recruitment strategies will include institutional email and flyers with links to study information. To support recruitment, we have identified clinical champions, providers from each of the affiliated centers, who will help answer any questions about the research study. We will use verbal and clinical feedback from the clinical champion to identify barriers and solutions for recruitment and document reasons for non-participation. Those meeting the inclusion criteria and interested in participating will provide informed consent and complete a demographic form prior to study participation.

#### Intervention description

2.3.4

Figure 3 provides a schematic of the *Bedtime Stories* program. The *Bedtime Stories*-*Provider* course is designed to be a self-paced, interactive course hosted on the (*blinded for review*) Center for Educational Excellence and Innovation website. Participants will receive a personalized link to the *Bedtime Stories-Provider* course. The course includes six required modules (Basics of Sleep, Sleep and Child Development, Sleep Health, Consequences of Deficient Sleep, Sleep Health Disparities, Sleep Screening and Referral Procedures in Clinical Practice) and one optional module on Melatonin Use in Children. The course includes module learning objectives, module quiz questions, and downloadable resources. The course will take approximately 2 $\frac{1}{2}$−3 h to complete the six required modules. Content and topic knowledge will be assessed throughout and at the end of the course using a retrospective pretest–posttest survey. The retrospective pretest–posttest survey is a preferred method to reduce response shift (Visser et al., 2000) and uses a five-point Likert scale (1-strongly disagree; 5-strongly agree) to assess knowledge and intent to change practice. Participants will also complete a course feedback questionnaire and receive continuing medical education (CME) credit and a $25 gift card upon completion of the course.

**Figure 3 F3:**
[figure not shown]
Design of the *Bedtime Stories* program and schematic of each intervention.

#### Outcome measures

2.3.5

We will assess the feasibility of implementing *Bedtime Stories-Provider* with participant recruitment (≥70%) and retention (retention ≥80% complete the course) targets. Adherence will be assessed by clinician completion rates. Fidelity will be assessed based on perceptions of the delivery of sleep guidance consistent with the RESTED framework during clinical encounters. Acceptability will be assessed via a post-course survey examining participants' satisfaction and relevance to clinical practice. Completion logs will be used to assess the participants' login frequency, time to complete the six required modules, and pass rate (the number of attempts to obtain 80% or more correct items per module quiz). Twenty-five participants completing all study milestones will be considered our target metric. Exploratory outcomes include pre–post change in topic knowledge across the six required modules, confidence in changing clinical practice, preferences for module topics, and satisfaction with course elements (e.g., videos, case studies, clinical pearls, text, quizzes, resources).

#### Data analysis

2.3.6

Descriptive statistics (means, frequencies, percentages) will be used to summarize feasibility and acceptability. Feasibility will be examined by recruitment and retention (proportion of providers who complete the course). Exploratory paired pre-post comparisons will be presented with 95% confidence intervals (Tonon et al., 2022). We will investigate exploratory analyses to assess possible differences between healthcare professions (MD, NP, PA). Course evaluations and feedback will assess the acceptability and preferences of course topics and course elements to inform future adaptations and iterations.

#### Ethical considerations

2.3.7

The *Bedtime Stories-Provider* study protocol is approved by the Institutional Review Board (P00044533) and registered with clinicaltrials.gov, NCT06455579 (version 2). Participants will provide informed consent electronically via RED Cap. Data confidentiality will be maintained in accordance with institutional standards. The results of this study will be presented at local, national, and international conferences and will be disseminated in peer-reviewed journals for publication.

### Aim 2. *Bedtime Stories-Caregiver* sleep health education for caregivers

2.4

The primary aim will examine the feasibility of the 6-week *Bedtime Stories-Caregiver* program (recruitment, retention, fidelity, adherence, engagement, and acceptability). Planned exploratory investigations will examine changes in caregiver sleep, knowledge, and self-efficacy. Additional analyses will assess possible influences of baseline caregiver stress and the child's sleep environment on caregiver and child sleep at follow-up.

#### Study design

2.4.1

A single-arm, pre–post feasibility pilot study of *Bedtime Stories-Caregiver*, a 6-week digital sleep health education intervention for caregivers of school-aged children.

#### Setting, recruitment, and eligibility criteria

2.4.2

Caregivers will be recruited from two community health centers affiliated with a large hospital in the Northeast. Eligible participants are caregivers of children aged 5–12 years who receive care at the affiliated health centers, are comfortable communicating in English, and live in the same household as the child. Due to known variations in sleep physiology and sleep needs, exclusion criteria include: (1) children with a neurodevelopmental, neurological, genetic, or other diagnosis affecting neurodevelopment; (2) children with an identified or diagnosed sleep disorder; and/or (3) families who are currently homeless. Caregivers will be identified through electronic medical records and contacted via email or recruited in person at the healthcare center.

#### Intervention description

2.4.3

As shown in the second row of Figure 3, once consented, caregivers will complete an onboarding survey about goals for their child's sleep (reasons for improving the child's sleep, goals, strategies, and anticipated challenges) and baseline questionnaires [PROMIS Sleep Disturbance and Sleep-Related Impairment short forms 8a, Perceived Stress Scale (PSS), and Knowledge, Attitudes, and Self-Efficacy Beliefs (KASB)] and for 1-week a daily digital sleep diary about their child's sleep. Beginning 1 week after baseline, for 6 weeks, caregivers will receive a weekly text message linking to a self-guided video module on one RESTED topic. In addition to the weekly video, participants will receive regularly scheduled reminders and check-ins. The video module reminders will be sent 3 days later if the video has not yet been viewed. Weekly check-ins will be sent 2 days after the video is viewed to promote engagement and gather feedback. Weekly check-ins will include brief questions about the child's sleep, perceived helpfulness of the content, and an opportunity for open-ended feedback for future adaptations. After 6 weeks, caregivers will complete follow-up questionnaires (via REDCap) and for 1 week, a daily digital sleep diary about their child's sleep. Participants will receive up to a $125 gift card upon completing study milestones (baseline, 6-weekly modules, follow-up).

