#### Aim 1. *Bedtime Stories*: providers sleep health education for PCCs

2.3.1

Table 2 summarizes the *Bedtime Stories* program aims and measures for each intervention. The primary aim is to assess the feasibility indicators (recruitment, retention, fidelity, adherence, engagement, and acceptability) of the *Bedtime Stories*: *Provider* online sleep health education course. An exploratory aim is to investigate changes in providers' knowledge and their intent to change clinical practice.

**Table 2 T2:** Program aims.

Aim	Construct	Measure	Variable and method details
Aim 1. *Bedtime Stories-Provider* sleep health education for PCC			
1a	Feasibility	Feedback and evaluation questionnaire (FEQ)	Feasibility indicators (Teresi et al., 2022; recruitment, retention, fidelity, adherence, engagement, and acceptability). 19-item questionnaire-total score. Assessed once post course completion.
1b	Knowledge	Content knowledge	Content knowledge and clinical performance (CME/MOC questions via online modules). Knowledge is assessed at the end of every module. There are 4–6 quiz questions per module. To pass the course, one must receive a score of 80 or above for each of the required modules (6 modules).
		Topic knowledge and practices survey	Each topic is assessed for change in knowledge. 11-item questionnaire-pre-post change. Assessed once post course completion.
Aim 2. *Bedtime Stories-Caregiver* sleep health education for caregivers			
2a	Feasibility and acceptability	User timestamps, weekly check-ins	Feasibility will be assessed by examining engagement (number of families consented), retention (proportion of families who complete all modules). Acceptability of the *Bedtime Stories* program will be assessed weekly with a 4-item questionnaire during the weekly check-in. The digital questionnaire was developed specifically for the *Bedtime Stories* Caregiver intervention to assess acceptability, feasibility and utility of module content and resources.

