#### Outcome measures

2.4.4

Feasibility outcomes of interest will include recruitment (the number of caregivers consented), retention (proportion of participants who complete all modules), engagement, and acceptability. We will assess the feasibility of participant recruitment and retention with the planned enrolment of 30-40 participants. Our target for completing all modules and follow-up surveys (≥75%) with satisfaction ratings (≥80%) will be used as benchmark metrics. Fidelity of the intervention will be assessed with a question following the weekly content. We will evaluate adherence by having participants complete at least 4 of the 6 weekly modules and by using follow-up questionnaires (PROMIS Sleep Disturbance and Sleep-Related Impairment short forms (caregiver and child), the Knowledge, Attitudes, and Self-Efficacy Beliefs (KASB) Questionnaire, and sleep diary). A sample of 20 participants completing all study milestones (baseline, weekly modules, and follow-up) will be used as the benchmark target. We will monitor participant engagement with logged timestamps and assess acceptability using weekly satisfaction check-ins (2–3 days after viewing the weekly content) to assess the satisfaction and usefulness of the module content. As an exploratory aim, we will examine pre-post changes in caregiver sleep, knowledge, and self-efficacy, and child sleep.

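### Aim 2: satisfaction is asked only of caregivers who have just watched a module, so the ≥80% benchmark carries no information from those who do not watch or who stop

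*Protocol article*

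**What the plan says.** Section 2.4.3 ties the check-in to viewing: "Weekly check-ins will be sent 2 days after the video is viewed to promote engagement and gather feedback". A caregiver who has not watched is described as getting something else: "The video module reminders will be sent 3 days later if the video has not yet been viewed". Section 2.4.4 makes the check-in the source of the acceptability data; the plan is to "assess acceptability using weekly satisfaction check-ins (2–3 days after viewing the weekly content) to assess the satisfaction and usefulness of the module content". Table 2 (row 2a) agrees, naming a four-item questionnaire inside the check-in.

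The benchmarks are also in section 2.4.4: "Our target for completing all modules and follow-up surveys (≥75%) with satisfaction ratings (≥80%) will be used as benchmark metrics". Around them stand the planned enrolment ("We will assess the feasibility of participant recruitment and retention with the planned enrolment of 30-40 participants") and a separate count of completers ("A sample of 20 participants completing all study milestones (baseline, weekly modules, and follow-up) will be used as the benchmark target"). The follow-up instruments listed there are the PROMIS forms, the KASB and the sleep diary. None of them measures satisfaction with the program.

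Section 2.4.5 summarises feasibility and acceptability descriptively. The article does not say what the 80% is a percentage of, or how up to six weekly ratings per caregiver become one figure.

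**The concern.** Acceptability is part of the primary aim of the caregiver study and has a numerical mark to meet. The rating is requested only after the behaviour that signals engagement, so whoever is asked in a given week has already engaged that week. A caregiver who drops out after module 2 leaves at most two early ratings, and one who never opens a video leaves none.

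This is fixed by the data collection and is not a detail that an analysis plan could settle later, because a rating that was never requested cannot be recovered. It also bears on the purpose of the pilot. Section 3.2 expects competing demands on caregivers and says the feasibility metrics are there to detect early barriers and refine the components. The caregivers who meet those barriers are the ones least likely to be asked.

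**Working it through.** **Inputs (section 2.4.4 unless noted).** Enrolment N = 30 to 40; completion target 75%; satisfaction benchmark 80%; completer count 20; six weekly modules (section 2.4.3). All confidence intervals are exact (Clopper–Pearson) 95% intervals.

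**Step 1: the plan's own figures.** The satisfaction benchmark has no derivation to reproduce. The completer count can be set against the completion target:
- 0.75 × 30 = 22.5, so 23; 0.75 × 35 = 26.25, so 27; 0.75 × 40 = 30.
- The stated 20 is 20/30 = 67%, 20/35 = 57% and 20/40 = 50%.

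So the count of 20 does not follow from the 75% target at any of these enrolments, and at N = 40 it is met with half the families lost.

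**Step 2: completion target just met.** Assume that only completers supply ratings. This is an illustrative extreme, since early ratings from those who leave are possible.
- N = 40, 30 raters: 24/30 = 80% (CI 61% to 92%); 24/40 = 60% of enrolled (CI 43% to 75%).
- N = 30, 23 raters: 19/23 = 83% (CI 61% to 95%); 19/30 = 63% of enrolled (CI 44% to 80%).

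The all-enrolled figures count non-raters as not satisfied. At N = 40, if all 10 non-raters were in fact satisfied, the figure would be (24 + 10)/40 = 85%. The data would be compatible with anything from 60% to 85%, a range that contains the 80% mark.

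**Step 3: half disengage.** N = 40, 20 raters: 16/20 = 80% (CI 56% to 94%); 16/40 = 40% of enrolled (CI 25% to 57%). The range for all enrolled is 16/40 = 40% to (16 + 20)/40 = 90%. Completion is 20/40 = 50%, so the ≥75% target fails, while the count of 20 is met.

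**Step 4: weighting if weekly ratings are pooled.** Pooling is an assumption, because the article gives no rule. Both cases take N = 40.
- 20 caregivers satisfied in all six weeks give 20 × 6 = 120 ratings. Another 20 rate week 1 as unsatisfactory and leave, giving 20 ratings. Pooled: 120/140 = 86%. Per caregiver: 20/40 = 50%.
- With the completion target met, 30 satisfied caregivers give 30 × 6 = 180 ratings and 10 dissatisfied caregivers give one each. Pooled: 180/190 = 95%. Per caregiver: 30/40 = 75%.

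In both cases everyone rated at least once, so early ratings from those who leave do not cure the problem under pooling. One value per caregiver does.

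**The case against.** - **The denominator is open.** A reader might infer that the article defines the 80% among responders only. It does not. A rule that counts non-responders against the benchmark is not excluded, and a condensed article may leave it to the full protocol. This stands for the denominator, but not for the trigger, which the article does state.
- **Disengagement is measured elsewhere.** A reader might infer that the benchmarks could be met together with half the families gone. The ≥75% completion target is in the same sentence and would fail; retention, adherence and logged timestamps would show the loss as well. This stands. Two limits remain: no rule says how the benchmarks combine, and a completion rate does not say whether those who left disliked the program.
- **Those who leave early can contribute.** Anyone who views a module and answers is counted, so what is missing is mainly the weeks after disengagement. The figures in steps 2 and 3 are therefore extremes.
- **A non-viewer cannot rate content.** Asking after viewing is natural for items on the module. Counting silence as dissatisfaction also merges acceptability with retention: 80% of 40 enrolled is 32, more than the 30 completers that the completion target requires. For that reason the all-enrolled figure should not be a condition for meeting the benchmark. It does not answer the case for asking non-viewers why they did not watch.
- **The direction of bias is not shown.** Families may leave for lack of time without being dissatisfied. This is fair, and the present trigger leaves no way to tell.
- **Aim 1.** A reader might extend the point to the provider course, whose feedback form is described as "19-item questionnaire-total score. Assessed once post course completion". Section 2.3.5 sets no satisfaction mark there, so the benchmark argument does not carry over.

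**Conclusion.** The point holds for Aim 2 in a limited form. Satisfaction is requested only after viewing, and no acceptability question is described for caregivers who do not view or who stop. A reported 80% could correspond to 60% of those enrolled at N = 40 with the completion target just met, if completers are the only raters and non-raters are counted as not satisfied. Under pooling, the figure can pass while the per-caregiver proportion does not. These sizes rest on the stated assumptions. The documents give no information on how those who leave would have rated the program, so an upward bias is plausible but not demonstrated. The pilot remains valid. This is a cheap improvement to a primary metric, and it has to be made while ratings can still be requested.

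**What to change.** 1. Send the check-in on a fixed day each week to every enrolled caregiver, with a response option for not having watched and the main reason. The questions on the child's sleep can be answered either way; the content items apply only to viewers.
2. Define satisfaction once per participant, for example as a mean rating at or above the positive category, and do not pool weekly ratings.
3. State that the ≥80% benchmark is assessed among responders, and report it with an exact 95% confidence interval. Always show beside it the number enrolled, the completion rate and, as a sensitivity figure only, the proportion satisfied among all enrolled.
4. In the same edit, reconcile the count of 20 completers with 75% of 30 to 40, which is 23 to 30.

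The cost is a changed message trigger, one extra response option and a companion figure that will look less favourable. Because the check-in is also meant to promote engagement, sending it to non-viewers adds a prompt to the program, and the program description should record this.

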#### Outcome measures

2.4.4

Feasibility outcomes of interest will include recruitment (the number of caregivers consented), retention (proportion of participants who complete all modules), engagement, and acceptability. We will assess the feasibility of participant recruitment and retention with the planned enrolment of 30-40 participants. Our target for completing all modules and follow-up surveys (≥75%) with satisfaction ratings (≥80%) will be used as benchmark metrics. Fidelity of the intervention will be assessed with a question following the weekly content. We will evaluate adherence by having participants complete at least 4 of the 6 weekly modules and by using follow-up questionnaires (PROMIS Sleep Disturbance and Sleep-Related Impairment short forms (caregiver and child), the Knowledge, Attitudes, and Self-Efficacy Beliefs (KASB) Questionnaire, and sleep diary). A sample of 20 participants completing all study milestones (baseline, weekly modules, and follow-up) will be used as the benchmark target. We will monitor participant engagement with logged timestamps and assess acceptability using weekly satisfaction check-ins (2–3 days after viewing the weekly content) to assess the satisfaction and usefulness of the module content. As an exploratory aim, we will examine pre-post changes in caregiver sleep, knowledge, and self-efficacy, and child sleep.

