#### Outcome measures

2.5.4

Feasibility will be investigated by book distribution rates and survey completion rates. Recruitment feasibility will be measured through the distribution-to-response ratio. We will track the proportion of book recipients who complete a one-time survey. The target sample will be 25 participants who complete all study materials. Acceptability will be assessed by caregiver report of their child's sleep and satisfaction with the book's content (≥80% positive ratings). Book engagement will be measured as ≥3 book readings per week to be considered acceptable engagement. Other outcome measures will include the frequency of shared reading, changes in the bedtime routine, and the sleep environment (e.g., presence of electronic devices in the bedroom).

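### Caregiver recruitment (Aim 2), a primary feasibility indicator, is defined only as a count of consents, so it does not give the uptake rate that planning the larger trial needs

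*Protocol article*

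**What the plan says.** The Method paragraph of the abstract places recruitment benchmarks among the program's primary outcomes. Section 2.4 lists recruitment first among the Aim 2 feasibility indicators.

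Section 2.4.4 then says what recruitment means for caregivers: "Feasibility outcomes of interest will include recruitment (the number of caregivers consented), retention (proportion of participants who complete all modules"). The next sentence supplies the reference figure: "We will assess the feasibility of participant recruitment and retention with the planned enrolment of 30-40 participants". Table 2 uses the same count under another name: "Feasibility will be assessed by examining engagement (number of families consented), retention (proportion of families who complete all modules").

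The other figures in 2.4.4 concern later steps. One sentence covers completion and satisfaction: "Our target for completing all modules and follow-up surveys (≥75%) with satisfaction ratings (≥80%) will be used as benchmark metrics". Another covers completers: "A sample of 20 participants completing all study milestones (baseline, weekly modules, and follow-up) will be used as the benchmark target".

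On how families are found, 2.4.2 says "Caregivers will be recruited from two community health centers affiliated with a large hospital in the Northeast" and "Caregivers will be identified through electronic medical records and contacted via email or recruited in person at the healthcare center". It gives neither the number of families contacted nor the size of the eligible pool.

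**The concern.** Section 3.3 says the feasibility data are to guide implementation before a fully powered trial. To plan that trial, one needs to know what share of the families who are contacted will enrol. That share drives the number of sites and the length of recruitment. It also indicates how self-selected the enrolled families may be, which matters for a program aimed mainly at low-income, racially and ethnically diverse families.

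A count of consents does not carry this information. It mixes the families' willingness with the effort spent contacting them, so the same enrolment can reflect high uptake from a short list or low uptake from a long one. Retention, defined in the same sentence, is a proportion; recruitment is not.

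**Working it through.** **Inputs from the article.** Recruitment measure: number consented (2.4.4; Table 2). Reference figure: 30-40 enrolled (2.4.4). Number contacted, consent rate and size of the eligible pool: not stated. The contact numbers and consent rates below are therefore assumptions, shown over a range.

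**The plan's own figure.** The article gives no derivation of 30-40, so there is nothing to reproduce. The nearest check is 20 completers at 75% completion: 20 / 0.75 = 26.7, so 27. The article does not present 30-40 as obtained in this way, and the point does not depend on it.

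**Step 1: what 30 consents can mean.** Rate = 30 / n contacted, with the Wilson 95% interval

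(p + z²/2n ± z·√[p(1−p)/n + z²/4n²]) / (1 + z²/n), z = 1.96.

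- n = 43: p = 0.698. Centre term 0.698 + 0.045 = 0.742; half-width term 0.144; divisor 1.089. Interval 0.549 to 0.814.
- n = 600: p = 0.050. Centre term 0.050 + 0.003 = 0.0532; half-width term 0.0177; divisor 1.0064. Interval 0.035 to 0.070.

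Exact (Clopper-Pearson) intervals are nearly the same: 54-83% and 3.4-7.1%. The two intervals are far apart, yet the recorded recruitment result is 30 in both cases.

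**Step 2: contacts expected for a given enrolment.** Contacts = target / consent rate, rounded up.

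| Assumed consent rate | For 30 consents | For 40 consents |
|---|---|---|
| 70% | 43 | 58 |
| 30% | 100 | 134 |
| 10% | 300 | 400 |
| 5% | 600 | 800 |
| 2% | 1,500 | 2,000 |

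**Step 3: how far the count follows contact volume.** P(X ≥ 30), with X binomial (n contacted, consent rate p):

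- p = 10%: 0.016 at n = 200; 0.53 at n = 300; 0.999 at n = 500.
- p = 5%: 0.18 at n = 500; 0.96 at n = 800; above 0.999 at n = 1,200.
- p = 2%: 0.02 at n = 1,000; 0.96 at n = 2,000.

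At a fixed willingness, the chance of reaching 30 moves from near 0 to near 1 with the number contacted. The low values also show that the count can fall short when the pool is limited.

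**The case against.** Several points on the other side have weight.

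- **No pass mark is written.** The article calls 30-40 the planned enrolment, and the sentence can be read as naming the sample in which recruitment and retention are studied. A reader might infer that recruitment is declared feasible once 30 consents are reached, and so passes automatically. The text does not state that rule. What stands is that the measure itself is a count, whatever rule is applied to it.
- **The count can disappoint.** A reader might also infer that it could never reveal infeasible recruitment. The pool is finite: two centers, one age band, three exclusions, a language requirement and a shared household. With 500 contacts at 5% consent, the chance of 30 consents is only 0.18. That stronger reading fails.
- **The article is condensed.** A limit on contacts or a recruitment period may stand in the full protocol, so their absence here is no fault. The definition of recruitment is different: it is stated, not left out. Section 2.4.5 mentions percentages for feasibility in general, which leaves room for a consent percentage but does not promise one.
- **The comparison with Aim 1 is limited.** Section 2.3.5 sets recruitment at ≥70% but does not say of what, so it does not prove that a consent rate was used there.
- **Aim 3 does not share the fault.** Its "The target sample will be 25 participants who complete all study materials" might suggest the same problem, but 2.5.4 measures recruitment by the ratio of books distributed to responses and labels 25 a target sample.
- **The denominator may need work.** The article mentions no contact log. A record list need not equal the eligible families, since co-residence and comfort in English may have to be asked.

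**Conclusion.** The point holds as a weakness in a stated definition. In 2.4.4 and Table 2, caregiver recruitment is a number without a denominator, and no other section supplies one. The same 30 consents are compatible with uptake of 70% (95% CI 55-81%) or 5% (95% CI 3.5-7.0%), and the measure as defined does not tell these apart. Both figures rest on assumed contact numbers (43 and 600); the binomial figures also assume independent consents at a constant rate. The conclusion needs only that the number contacted is not part of the measure.

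The enrolment target itself is not at fault, and the pilot can still show a recruitment shortfall. What it lacks, as defined, is the uptake rate for planning the larger trial. The change should be made: recruitment is a primary feasibility indicator and the repair is cheap.

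**What to change.** In 2.4.4, define Aim 2 recruitment as caregivers consented divided by caregivers contacted or approached and, where eligibility is known, divided by eligible caregivers as well. Report it with a 95% CI and separately for the email and in-person routes. Base the recruitment feasibility judgement on that proportion and keep 30-40 as the sample-size target only. Change the Table 2 entry to match and use one label for the quantity, since it is now recruitment in one place and engagement in the other.

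Cost: a revised sentence in 2.4.4, a matching edit in Table 2, and a running tally of emails sent and in-person approaches. No participants are added and the intervention is unchanged. Eligibility may be unknown for some contacted families, so the contacted and eligible denominators may differ and both should be shown. The reported result may look less favourable than a count.

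### Caregiver study: the benchmark of 20 completers is only 50–67% of the planned enrolment and does not match the ≥75% completion benchmark, and the text does not say which governs

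*Protocol article*

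**What the plan says.** Section 2.4.4 (Outcome measures, Aim 2) gives these elements in one paragraph:

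- Planned size: "We will assess the feasibility of participant recruitment and retention with the planned enrolment of 30-40 participants".
- Retention: "retention (proportion of participants who complete all modules".
- A proportional benchmark: "Our target for completing all modules and follow-up surveys (≥75%) with satisfaction ratings (≥80%) will be used as benchmark metrics".
- A count: "A sample of 20 participants completing all study milestones (baseline, weekly modules, and follow-up) will be used as the benchmark target".
- A separate, looser criterion labelled adherence: "We will evaluate adherence by having participants complete at least 4 of the 6 weekly modules".

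Section 2.4.3 (Intervention description) confirms what the milestones are when it describes payment: "upon completing study milestones (baseline, 6-weekly modules, follow-up". In that section both baseline and follow-up include a week of daily sleep diaries.

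The paragraph does not derive 20 from 75%, does not rank the two, and does not say how a result meeting only one is to be read. The Abstract names recruitment and retention benchmarks among the program's primary outcomes. Section 2.4.5 plans a descriptive analysis of feasibility.

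**The concern.** The percentage and the count are both called benchmarks, and both measure finishing the modules and the follow-up. If they are meant as two expressions of one target, they should coincide somewhere in the planned enrolment range, and they do not. The count is the lower hurdle at every planned size.

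What is at stake is how a primary feasibility outcome is read. Twenty completers out of 40 could be reported as having reached the benchmark target although half of those enrolled did not finish. The same data could be reported as falling well short of the completion benchmark. Section 3.3 says the feasibility data will guide implementation before a fully powered efficacy trial, so the reading matters for what follows. If the choice between the benchmarks is left until results are known, that choice settles the conclusion.

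**Working it through.** **Inputs**, all from section 2.4.4: planned enrolment N = 30 to 40; completion benchmark 75%; completer benchmark 20.

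**Step 1. Can 20 be reproduced from the plan's own figures?** The completers needed for 75% are 0.75 × N, rounded up. The rate implied by the count is 20 / N.

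| N | 0.75 × N | Completers needed | 20 / N | Results meeting 20 but missing 75% |
|---|---|---|---|---|
| 30 | 22.5 | 23 | 66.7% | 20–22 |
| 35 | 26.25 | 27 | 57.1% | 20–26 |
| 40 | 30 | 30 | 50.0% | 20–29 |

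The figure of 20 is not reproduced at any planned size. The nearest value is 23, at N = 30.

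**Step 2. The inverse.** 20 / 0.75 = 26.7. Checking whole numbers, 20/26 = 76.9% passes and 20/27 = 74.1% fails. Twenty completers therefore satisfy the 75% benchmark only with 26 or fewer enrolled, four below the planned minimum.

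**Step 3. Do the definitions differ enough to remove the conflict?** The percentage covers all modules and the follow-up surveys. The count adds baseline and, depending on how surveys is read, the diaries. Anyone who completes all milestones has completed the modules and follow-up, so the milestone count cannot exceed the module-and-follow-up count. If both counts are 20, the count benchmark passes and the percentage fails at every N from 30 to 40. The 4-of-6-modules criterion is labelled adherence and enters neither benchmark.

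**Step 4. How likely is a split?** The documents give no expected completion rate, so the rates p below are assumptions. Both benchmarks are taken to apply to the same completers, X ~ Binomial(N, p), and the split probability is P(X ≥ 20) − P(X ≥ completers needed).

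| Assumed p | N = 30 | N = 40 |
|---|---|---|
| 60% | 0.291 − 0.044 = 0.25 | 0.926 − 0.035 = 0.89 |
| 70% | 0.730 − 0.281 = 0.45 | 0.998 − 0.309 = 0.69 |
| 75% | 0.894 − 0.514 = 0.38 | 1.000 − 0.584 = 0.42 |
| 80% | 0.974 − 0.761 = 0.21 | 1.000 − 0.839 = 0.16 |
| 90% | about 0.01 | about 0.001 |

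A split is likely if true completion lies around 60–75% and unlikely if it is near 90%.

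**The case against.** The best defence is that a lower count beside a stricter rate is not a contradiction in itself. Both can be required together, in which case the 75% simply binds. Twenty may be meant as the smallest complete-data sample worth analysing. The sister studies lend this some support: section 2.5.4 speaks of a target sample of 25 who complete all materials, and section 2.3.5 gives a count of 25 alongside rates of 70% and 80%. This reading is possible, but section 2.4.4 does not state it. It calls 20 the benchmark target for completing all milestones, in the same paragraph as the other benchmark. What stands is that the fault may lie in the labelling and not in the number.

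A second defence is that the milestone definition is stricter. If the diaries count towards milestones but not towards surveys, 20 full completers could coexist with 23 or more module-and-survey completers. That narrows the conflict, but split results remain possible.

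A third is that an article condenses a fuller protocol. That would excuse an omission. Here the article states two figures that do not fit together.

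A reader might also infer that recruitment has the same fault, because it is defined as a count of consents with no denominator. The documents do not support that. The count contradicts no other figure in the caregiver study. Some caregivers are recruited in person, and screening denominators are commonly left to a full protocol. A consent rate would be a design preference, and it is not part of this point.

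**Conclusion.** The point holds as an unreconciled pair of thresholds for one of the program's primary feasibility outcomes. The count of 20 corresponds to 50–67% of planned enrolment against a stated 75%, a shortfall of 3 completers at 30 enrolled and 10 at 40. This part rests only on the document's own figures, with the 75% taken over enrolled participants, as the retention definition indicates. Only a denominator of 26 or fewer would reconcile the two. The split probabilities rest in addition on assumed completion rates and on treating both definitions as the same event.

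A reader might infer that this invalidates the study or must be corrected before it can proceed. The documents do not support that. The study is a single-arm pilot with descriptive analysis, section 2.4.4 states no progression rule, and no error rate depends on either benchmark. If count and percentage are both reported, readers can see any disagreement for themselves. It should be fixed because the fix is cheap and removes a choice that would otherwise be made after the results are known.

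**What to change.** Before any outcome data are seen, amend section 2.4.4 as follows:

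1. State that completion of all modules and follow-up surveys by at least 75% of consented caregivers is the governing completion criterion.
2. Do one of two things with the count. Either restate it to agree with 75%, as 23 completers if 30 enrol rising to 30 if 40 enrol, or keep 20 and relabel it as a minimum complete-data sample that is not a criterion of feasibility success.
3. Say whether the sleep diaries count towards completion, so that the percentage and the count refer to a known set of tasks.

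The cost is wording only, with no new data and no change to enrolment. If the count is restated, the completer target becomes less favourable to the study (23–30 instead of 20).
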